**Table 1 Tab1:**
[figure not shown]
Schedule of enrolment, interventions, and assessments

Follow-up visits are planned post-surgery. Pain assessment: score for pain around the implant; radiating pain; headache associated with implant. Cosmetic result scores: score for natural skin position, baldness, scarring, skin color, indentation, overall cosmetic score. Light gray chart indicates measurements assessed at follow-up visits/extra consultations with a Holgers Index score ≥ 2

*RFA:ISQ* Resonance Frequency Analysis: Implant Stability Quotient, *HUI3* Health Utilities Index Mark 3, *APHAB* Abbreviated Profile of Hearing Aid Benefit, *ICECAP-A* ICEpop CAPability measure for Adults, *N.A*. not applicable, *IS-pro* a 16S-23S rDNA interspace (IS) region-based profiling method

^*^Outcome measurements obtained at Maastricht University Medical Center only

ˇOnly after explicit additional informed consent

### Study interventions and allocation

All participants will undergo single-stage surgery to receive a 4-mm Ponto wide implant with mounted abutment (Oticon Medical AB, Askim, Sweden), which will be performed by an experienced ENT surgeon. Four abutment lengths are available: 6, 9, 12 and 14 mm. Subjects will be randomized to the test group (MIPS technique [26]) or the control group (linear incision technique with soft tissue preservation [24]) in the order in which they enter the study. Skin thickness is a possible factor that could influence inflammation, but this is measured during surgery, making it impossible to stratify for skin thickness prior to surgery. Considering that men are known to have significantly thicker skin than women [40], group allocation is stratified for gender. Researchers will randomize each subject using randomization software (Statistiska Konsultgruppen, Gothenburg, Sweden), which will be performed in each research center independently in a 1:1 ratio for the test and control group stratified for gender until the total number of 62 participants has been reached. Due to clear differences in surgical techniques, it is impossible to blind the surgeon, researcher or subject. In short both surgical techniques are described here:

#### Control group (linear incision technique with soft tissue preservation) [24, 41]

The intended implant position is marked (Fig. 1a). (I) A retroauricular linear incision is made down to the periosteum that is subsequently opened to expose the periosteum posterior to the incision line (Fig. 1b). (II) At the intended implant site, a central area of periosteum is removed. (III) An initial 3-mm-deep hole is created using a guide drill. (IV) If there is still bone at the bottom of the initial hole, it is deepened to 4 mm using the same drill by removing a spacer. (V) To prepare the initial hole for implant insertion it is widened with a countersink drill. (VI) The implant with mounted abutment is installed with a torque setting of 40–50 Ncm. (VII) The skin is retracted over the abutment and dermal sutures are placed. (VIII) The abutment is recovered by punching the skin with a 5-mm punch. (IX) A healing cap is attached to the abutment and gauze drenched in an antibiotic ointment is applied.

**Fig. 1 Fig1:**
[figure not shown]
Surgical implantation techniques. **a** Implant positioning. **b** Schematic presentation of the linear incision technique with soft tissue preservation. (I) Linear incision. *(II)* Opening of skin. *(III)* Initial hole drilling. *(IV) C*ountersink drilling. *(V)* Eccentric skin punch to uncover abutment. *(VI)* Result. **c** Schematic presentation of Minimally Invasive Ponto Surgery (MIPS) technique. *(I)* Incision hole. *(II)* Removal of periost and soft tissue*. (III)* Placement of cannula. *(IV)* Drilling procedure (cannula guide drill and cannula widening drill). *(V)* Implant placement with the insertion indicator. *(VI)* Result

#### Test group (MIPS technique) [26, 42]

The intended implant position is marked (Fig. 1a). *(I)* An incision is created with a 5-mm punch at the intended implant site (Fig. 1c). *(II)* The periosteum and remaining soft tissue around the incision hole are removed with a raspatorium. *(III)* The cannula is inserted at the surgical site. *(IV)* A 3-mm hole is created initially with the cannula guide drill. *(V)* If there is bone at the bottom of the 3-mm hole, it is deepened to 4 mm using the same drill by removing a spacer*. (VI)* To prepare the initial hole for implant insertion, it is widened with the cannula widening drill. *(VII)* The cannula is removed and subsequently the implant with mounted abutment is installed with a torque setting of 40–50 Ncm*. (VIII)* To help estimate complete insertion of the implant, an installation indicator is attached to the abutment inserter, which makes it possible for the surgeon to count the number of rotations. This step was added during the course of the study. *(IX)* A healing cap is attached to the abutment and gauze drenched in an antibiotic ointment is applied.

### Follow-up

Follow-up visits for all participants are scheduled at 9 days, 21 days, 3 months, 1 year and 2 years post-surgery (Fig. 2). During this period all extra consultations are captured in high detail. The consultations are largely comparable to standard visits (Table 1). By compiling extra consultation visits and regular follow-up visits, we can present a more accurate estimate of common complications that can occur at any time point.

**Fig. 2 Fig2:**
[figure not shown]
Study design and study flow chart

### Outcomes

#### Primary outcome

The primary outcome of this study is the incidence of inflammation (episodes of PAD) between surgery and 3 months post-surgery. During each visit, the peri-abutment skin is graded based on the Holgers Index. The Holgers Index is a five-point scale described by Holgers [11]: “0 no irritation; 1 slight redness; 2 red and slightly moist tissue, no granuloma formation; 3 reddish and moist; sometimes granulation tissue; 4 removal of skin-penetrating implant necessary due to infection” [11]. In this study, inflammation has been defined as the occurrence of a Holgers Index ≥ 2 as this often requires substantial treatment (e.g., systemic antibiotics or local intervention).

#### Secondary outcomes

Secondary outcomes include surgical procedure time, wound healing, presence of dehiscence after surgery, soft tissue height, loss of skin sensibility, pain, cosmetic results, implant stability quotient (ISQ) values, and extrusion rate (Table 1).

Surgical procedure time consists of the length of surgery (from the incision until the placement of the healing cap) and the total time spent in the operating theater by the subject (entering theater until leaving theater) in minutes. Both timings are measured using a stopwatch and are included because the preparation and post-surgical care can differ. Wound healing is evaluated during standard follow-up visits and can be graded as complete, partial or incomplete. The presence of dehiscence is evaluated at all visits. Soft tissue height and overgrowth is assessed by measuring the distance from the top of the abutment to the skin in four quadrants. Numbness is measured as the start of sensibility from the abutment to the most outward diameter. Pain is assessed for three separate domains including pain directly around the abutment, radiating pain, and headache that is related to the BCHI. Pain is graded in a 10-point scale with a scale of 0 representing “no pain” to 10 representing “the worst pain imaginable”. Cosmetic results are assessed by the surgeon using several properties which were thought to be influenced by the surgical technique. These included the folding of the skin around the abutment, baldness, scarring, skin color, indentation, and an overall cosmetic score as assessed by the surgeon and subject. All results are graded on a 10-point scale and compared to the contralateral side if applicable. ISQ values are obtained with the Ostell ISQ equipment (Ostell, Gothenburg, Sweden) by mounting a Smartpeg Type 55 on the abutment and obtaining two perpendicular ISQ values at all visits. All cases of abutment exchanges and implant extrusion are noted (time of extrusion, reason if known and subsequent action).

#### Tertiary outcomes

##### Quality of life and economic evaluation

Three questionnaires are used to evaluate the impact on hearing-specific and generic quality of life and capabilities. The questionnaires are filled in at baseline, at 1-year follow-up, and at 2-year follow-up. The Abbreviated Profile of Hearing Aid Benefit (APHAB) is a 24-item self-assessment, disability-based inventory, designed for hearing-related quality of life [43]. Each item is assessed in both the unaided and aided situation. The Health Utilities Index Mark 3 (HUI3) is a preference-based system for measuring generic health-related quality of life, consisting of 17 questions [44]. It provides descriptive evidence on multiple dimensions of health status, including overall health and several health dimensions. These dimensions include: vision, hearing, speech, ambulation/mobility, pain, dexterity, self-care, emotion, and cognition. Each dimension has three to six discriminatory levels, making it sensitive to health changes induced by interventions [45]. The ICEpop CAPability measure for Adults (ICECAP-A) was designed [46] to measure capabilities [47]. Capabilities represent the “freedom” of an individual to “achieve” a certain functioning, without the need to have actually achieved this [48]. This 5-point questionnaire has been translated and validated in Dutch [49]. It specifically assesses the capabilities attachment, security, enjoyment, role, and control. These questions include aspects such as independence, dignity, comfort, and social interaction, which might be influenced by hearing loss and subsequent interventions. A last tertiary objective of this study is a full economical evaluation after data has been collected for 1 year as we assume that 1 year after surgery, the complication rate, benefits, satisfaction, and BCHI processor usage are stable in both treatment groups. Cost will be identified at each study visit using the case report form (CRF), which is designed to identify costs. We will perform a cost-utility analysis, with the quality-adjusted life year calculated from the obtained HUI3 scores as the outcome. The analysis will be executed using a societal perspective. The evaluation will be performed according to the standards and guidelines of the International Society for Pharmacoeconomics and Outcomes Research (ISPOR) [50].

#### Exploratory outcomes

##### Skin displacement

High-resolution photographs (MUMC+: Nikon D800E, Nikon Corp., Tokyo, Japan) with an additional lens (Nikon AF-S VR Micro-Nikkon 105 mm f/2.8G IF-ED, Nikon Corp., Tokyo, Japan); ZGT and MCL: iPhone 6 (Apple Inc., Cupertino, CA, USA) are collected at surgery and follow-up visits. These photographs can be used to evaluate the peri-abutment skin over time and to assess the skin movability in relation to movements of the head and jaw using standardized skin markings. These photographs will also be used to study the validity of the Holgers Index and to investigate peri-abutment dermatitis. In addition, the minimal and maximal size of the gap between the abutment and skin is measured in all quadrants.

##### Etiology of peri-abutment dermatitis

These outcome measures are obtained at MUMC+ only. Skin biopsies of the implantation site are obtained during surgery, at 3 months post-surgery, and during episodes of inflammation if participants have explicitly provided an additional written informed consent for this procedure. RNA will be extracted from the biopsies and subsequently cDNA will be synthesized. We intend to determine mRNA expression of 15 selected genes (Table 2) using real-time reverse transcription polymerase chain reaction. Pre-surgical mRNA expression (baseline) and post-surgical expression will be compared. Specific profiles related to inflammatory responses, tissue remodeling, vascularization, and bacterial infection will be assessed.

**Table 2 Tab2:** Overview of cytokines

Inflammatory mediators	TGF- ß MIP-1α	Microbial infection
IL-1ß		TLR-2
IL-6	Tissue remodeling	TLR-4
IL-8	MMP-9	
TNF-α	TIMP-1	Vascularization
IL-17	COL1 α1	VEGF-A
IL-10		FGF-2

*IL* interleukin, *TNF-α* tumor necrosis factor alpha, *TGF-ß* transforming growth factor beta, *MIP-1 α* macrophage inflammatory protein 1 alpha, *MMP-9* matrix metalloproteinase 9, *TIMP-1* tissue inhibitor of metalloproteinase 1, *COL1 α1* collagen, type 1, alpha 1, *TLR* Toll-like receptor, *VEGF-A* vascular endothelial growth factor A, *FGF-2* basic fibroblast growth factor-2

Bacterial swabs of the abutment, peri-abutment skin and contralateral skin are collected during the same time points. The bacterial content will be evaluated with IS-pro, a novel 16S-23S rDNA interspace (IS) region-based profiling method [51]. This method is devised to enable high-throughput molecular profiling of any microbiota. The combined data sets will be used to study peri-abutment dermatitis and validate the Holgers Index.

### Analysis

#### Sample size calculation

The incidence of inflammation, a Holgers Index ≥ 2, between surgery and 3 months post-surgery will be compared between both groups. The sample size is calculated using the concept of effect size (ES) as presented by Lerman and Cohen [52, 53]. The proposed test concerns a two-sample test for binomial proportions, which is equivalent to a Yates corrected chi-square test for a 2 × 2 contingency table. When taking into account a type 1 error level (α) of 0.05 and a power (1-β) of 0.8, the required sample size per group is: *n = 2(zα + zβ)*
^*2*^
*/ES*
^*2*^ 
*= 2(1.65 + 0.84)*
^*2*^
*/ES*
^*2*^ 
*= 12.4/ES*
^*2*^
*.* Assuming an ES index of *medium to large* with ‘h’ of 0.65 to discriminate between two proportions, the sample size is: *n = 12.4/h*
^*2*^ 
*= 12.4/0.65*
^*2*^ 
*= 29.4*. With an expected 5 % drop-out rate, 31 participants are needed per group, resulting in a total sample size of 62 participants.

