Although successful, the BCHI has complications. Known problems include skin inflammation, also known as peri-abutment dermatitis (PAD), pain, numbness of the skin around the implant, skin overgrowth, and implant loss [10]. PAD is graded on a five-point scale called the Holgers Index [11] and is perceived as the most common complication of BCHI use with an estimated occurrence of 16.1–38.1 % among all recipients [10]. PAD is an inflammatory process that is presumed to be multifactorial and little is known about the precise etiology of this condition [12]. Shear stress on the skin around the abutment [2, 13] sets on as the implant and abutment combination fixed to the skull is immovable. This may cause tearing of the skin (e.g., while turning on a pillow at night or during head and jaw movements). The implant and abutment are made of titanium, which may elicit a foreign body response [12, 14]. Also the formation of a biofilm on the abutment by bacteria that colonize the wound site due to persistent breach of the skin might play an important role [15, 16]. Another side effect of the BCHI is pain. This is frequently experienced by patients [17], however the exact cause for this, sometimes chronic pain, remains unknown [18–20]. Another condition which has anecdotally been observed is skin sagging, the presence of excess skin cranially to the abutment [21]. This might be problematic as it can influence the sound processor coupling and the proper function of the processor.

Various strategies for reducing complication rates with BCHIs have been employed throughout the years. Traditionally, the skin surrounding the abutment was thinned, but van de Berg et al. noted lower complication rates after BCHI surgery with a less invasive approach [20]. Since then, an even less invasive, single-stage procedure, where the soft tissue surrounding the abutment is left intact [22–25], has become one of the most common techniques used for BCHI surgery. Advantages of this tissue-preserving approach include: less surgical procedure time, reduced numbness or pain and better cosmetic results [22, 24, 25].

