#### Statistical analysis

This study is designed to include several endpoints including short-term results (3 months follow-up), long-term results (2 years follow-up), and an economic evaluation. Short-term results will be evaluated after all participants have reached 3 months follow-up and will describe the primary endpoint and secondary endpoints between surgery and 3 months follow-up. The primary endpoint will be described by comparing the proportions of inflammation between surgery and 3 months follow-up using a chi-square test. Long-term results will also be used for the economic analysis. Prior to analysis, a statistical analysis plan (SAP) will be created describing the method of analysis specifically for each endpoint.

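### The sample size section equates the primary test with a Yates-corrected chi-square, but its formula sizes the uncorrected test; with about 30 per arm, Yates would roughly halve the type 1 error and miss the stated 80% power

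*Protocol article*

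**What the plan says.** Two places in the Protocol article describe the test for the primary endpoint, the proportion of participants with a Holgers Index of 2 or more between surgery and 3 months.

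- *Sample size calculation*: the proposed test is a "two-sample test for binomial proportions, which is equivalent to a Yates corrected chi-square test for a 2 × 2 contingency table". The section then takes a "type 1 error level (α) of 0.05 and a power (1-β) of 0.8", uses n = 2(zα + zβ)²/ES² with zα = 1.65 and zβ = 0.84, and sets Cohen's h at a value "of 0.65 to discriminate between two proportions". This gives 29.4 per group, and with 5% drop-out 31 per group and 62 in total.
- *Statistical analysis*: the primary endpoint is described by "comparing the proportions of inflammation between surgery and 3 months follow-up using a chi-square test". No continuity correction is mentioned or excluded. A SAP giving the method for each endpoint is to be written before analysis.

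**The concern.** The square of the pooled two-sample z statistic for proportions is the uncorrected Pearson chi-square. It is not the Yates statistic, which subtracts a continuity term first. The stated equivalence is therefore wrong, and it conflicts with the formula in the same paragraph, which contains no such term.

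In a large trial this would hardly matter. With about 30 per arm and modest event rates, the correction makes the test markedly conservative. An analyst who follows the sample size section as written would run a test with neither the stated alpha nor the stated power. The later section does not say which version decides the trial. The choice matters more because the surgeon, researcher and participant all know the allocation.

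**Working it through.** **Inputs.** From *Sample size calculation*: alpha 0.05, power 0.80, zα = 1.65, zβ = 0.84, h = 0.65, 5% drop-out, 31 per group. From *Study interventions and allocation*: 1:1 allocation. From *Background*: an "estimated occurrence of 16.1–38.1"% for peri-abutment dermatitis among all recipients. The protocol gives no planning rate per arm, so that range is an assumption here.

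**Step 1: reproduce the stated size.** 2(1.65 + 0.84)² = 12.40. Then 12.4/0.65² = 29.35, which the protocol gives as 29.4. Then 29.35/0.95 = 30.9, so 31 per group and 62 in total. The figure reproduces with no continuity term and with a one-sided 5% quantile.

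**Step 2: the two statistics.** For a and b events and c and d non-events in two arms of n each, with N = 2n and m = a + b:

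- Pearson: X² = N(ad − bc)²/[n²·m·(N − m)]
- Yates: X² = N(|ad − bc| − N/2)²/[n²·m·(N − m)]

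Example with 31 per arm, 12 v 5 events: |ad − bc| = |12·26 − 5·19| = 217, and the denominator is 31²·17·45 = 735,165.

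- Pearson: 62·217²/735,165 = 3.97, p = 0.046
- Yates: 62·(217 − 31)²/735,165 = 2.92, p = 0.088

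The 5% critical value is 3.84, so the verdict changes. Likewise 10 v 3 gives p = 0.029 and 0.061, and 11 v 4 gives 0.038 and 0.075.

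**Step 3: true type 1 error.** All 2 × 2 tables were enumerated with equal binomial rates in both arms. The table gives the range over common rates of 16.1% to 38.1% at two-sided 0.05.

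| n per arm | Uncorrected | Yates |
|---|---|---|
| 29 | 4.6% to 5.2% | 1.8% to 2.5% |
| 30 | 4.8% to 5.2% | 1.9% to 2.6% |
| 31 | 5.0% to 5.2% | 1.9% to 2.6% |

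At the one-sided cut-off with 31 per arm, the uncorrected size is 4.7% to 5.6% and the Yates size 2.1% to 2.9%.

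**Step 4: power if h = 0.65 is true.** The second-arm rate is sin²(arcsin √p − 0.325), where p is the control rate. Each cell gives the range over 29 to 31 per arm. One-sided means z = 1.65, with rejection only in favour of the lower-rate arm.

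| Control v second arm | Uncorrected, one-sided | Yates, one-sided | Uncorrected, two-sided | Yates, two-sided | Tests disagree, two-sided |
|---|---|---|---|---|---|
| 16.1% v 0.8% | 79–82% | 44–50% | 63–67% | 27–32% | 35% |
| 25% v 3.9% | 81–83% | 62–66% | 70–73% | 48–53% | 20–22% |
| 30% v 6.3% | 81–83% | 65–70% | 69–72% | 53–58% | 14–16% |
| 38.1% v 11.1% | 81–83% | 69–73% | 68–72% | 57–60% | 11–12% |

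The uncorrected one-sided column recovers the planned 80%, which confirms that this is the test the formula sizes. Yates misses 80% in every row.

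**Step 5: sidedness.** With 1.96 in place of 1.65, the same formula gives 2(1.96 + 0.84)²/0.65² = 37.1, and 37.1/0.95 = 39.1, so 40 per group. This is why the uncorrected test at two-sided 0.05 falls short of 80% with 31 per group.

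**The case against.** The strongest reply is that the two sections do not truly conflict. A Yates-corrected chi-square is still a chi-square test, so the analysis section can be read as shorthand for the test specified just before it. A promised SAP is also the usual place to settle a continuity correction. This stands in part. A reader might infer that the protocol prescribes two opposite tests, but the analysis section never says uncorrected, so the documents do not support that. The SAP commitment also limits the room for choosing the test after seeing the result, although writing it before analysis is weaker than writing it before any data are seen in an open trial. What the reply does not remove is the error inside the sample size section, where the named test and the formula do not match.

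A second reply is that the largest disagreement figure, about 35%, is a corner case. That is right. It needs a 16.1% control rate and a second-arm rate of 0.8%. About 97% to 98% of such trials have an expected cell count below 5, where an uncorrected chi-square is conventionally avoided. The figure should not be used as a headline.

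A third reply is that Yates is merely conservative and inflates no false-positive claim. This is also true. The cost of Yates is lost power, in a trial whose own limitations section calls its small sample a major drawback.

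**Conclusion.** The concern holds in limited form. The Yates equivalence is wrong and does not fit the formula that produced 62 participants, and the analysis section does not resolve it. If Yates were used, the true two-sided type 1 error would be about 1.8% to 2.6% instead of about 5%. Power at the formula's own one-sided cut-off would be about 65% to 73% at control rates of 30% to 38%, and as low as 44% at 16.1%. At control rates of 25% to 38%, the choice of test would change the two-sided verdict in about 11% to 22% of trials.

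These figures assume that h = 0.65 is true, that 29 to 31 per arm are analysed, and that 3-month event rates fall in the background range. They shift outside it: at a 5% common rate with 31 per arm, the two-sided sizes are 3.0% uncorrected and 0.2% Yates.

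A reader might also infer that dropping Yates restores the planned 80% power at two-sided 0.05. It does not. The uncorrected test matches the formula on continuity only, and at two-sided 0.05 its power is about 63% to 73%. The shortfall under a two-sided Yates test therefore has two sources, the correction and the one-sided quantile.

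**What to change.** Delete the statement that the proposed test is equivalent to a Yates-corrected chi-square. Name one primary test in both sections, the two-proportion (chi-square) test without continuity correction, and fix it in the SAP before the 3-month data are analysed. If the SAP stratifies the primary analysis, use the stratified form, also without correction.

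State the sidedness in the same sentence. If the test is two-sided at 0.05, restate the power for 31 per group, because the 80% figure rests on a one-sided quantile.

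The cost is a sentence or two of text and no extra data. The small downside is that the uncorrected test can slightly exceed 5%: about 5.2% two-sided in the range examined, and 5.6% at a 50% rate with 31 per arm. Keeping Yates instead would require a larger trial. By a sample size formula on the proportions themselves, continuity correction raises the one-sided requirement before drop-out from 32 to 40 per arm (30% v 6.3%) or from 31 to 38 (38.1% v 11.1%).

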The decision to choose one intervention over the other in a health care system *with limited resources* depends on the associated (clinical) benefits, but also on the incurred additional costs or cost savings. As reviewed by Crowson et al. [4], only a few investigations addressed the cost-effectiveness of a BCHI intervention, resulting in uncertainty regarding cost-effectiveness. One retrospective study by Monksfield et al. has been executed in the United Kingdom that compared gain in quality-adjusted life years to BCHI-related costs. Costs included: implantation surgery, post-surgical care, the first processor, annual check-up, processor maintenance, and processor replacement costs after 3 years [5]. This study concluded that the BCHI is probably cost-effective. So far, no study included non-health care costs, such as loss of productivity, travel costs and out-of-pocket costs.

In this article, we describe the research protocol for a multicenter randomized controlled study comparing the new MIPS technique to the linear incision technique with soft tissue preservation [24, 26] comparing the incidence of inflammation as primary objective. In this trial, revised parameter scales are introduced to quantify factors such as loss of skin sensibility, dehiscence of the skin next to the abutment, skin overgrowth, and cosmetic results. These are modified to reduce the subjective interpretation and are intended to be validated. For exploratory outcome measures related to PAD such as skin biopsies, bacterial swabs are collected. An economical evaluation is planned with quality of life approached from a capability perspective as well. The MIPS technique is hypothesized to result in a lower incidence of inflammation compared to the linear incision technique with soft tissue preservation.

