### Protocol amendments

After initial approval (protocol version 1.2 dated 4 November 2014), the study site opened for accrual on 1 December 2014. So far, the ethics committee has approved two substantial amendments to the study protocol. In June 2015, an amendment (protocol version 1.4 12 May 2015) was approved to increase the total number of participants from 42 to 62, resulting in a decrease of the ES from 0.8 to 0.65 with 80 % power to discriminate between two proportions. In the same amendment, in order to include sufficient participants, the study was expanded from a single-center study to a multicenter study. In October 2015, the second amendment (protocol version 1.5 11 August 2015) was approved to include MIPS surgical equipment update, based on feedback after the first surgeries. The alterations in MIPS surgical package included shortening of the cannula and the addition of wings in order to increase the grip and stability of the cannula. The guide drill was also modified, resulting in a wider drilling hole making it easier to manually feel the drilling hole with the widening drill. An installation indicator was also developed, to assist in visual feedback for insertion completeness by counting the number of rotations during insertion. These updates were incorporated as MIPS became available to multiple centers around the world and surgeons provided feedback in relation to their individual outcomes. These updates are not expected to affect the primary endpoint in a significant way, hence no change in the number of participants was necessary for this amendment. The change in the surgical procedure might influence secondary outcome measures (e.g., surgery time, risks on complications such as incomplete insertion) to a limited extent. All MIPS surgeries will be analyzed as one pooled treatment group but the number of participants per MIPS version will be reported on.

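### The sample size uses the one-sided value 1.65, but the named chi-square test at 0.05 is two-sided: 62 participants give about 70% power, not 80%

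*Protocol article*

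**What the plan says.** The sample size section of the protocol article sets "a type 1 error level (α) of 0.05 and a power (1-β) of 0.8". It computes n per group as 2(1.65 + 0.84)²/ES² = 12.4/ES² and takes an effect size h "of 0.65 to discriminate between two proportions", which gives 29.4 per group. "With an expected 5 % drop-out rate", this becomes 31 per group and 62 in total. The section describes the test as a two-sample comparison of binomial proportions, "which is equivalent to a Yates corrected chi-square test for a 2 × 2 contingency table".

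The statistical analysis section plans the primary analysis as "comparing the proportions of inflammation between surgery and 3 months follow-up using a chi-square test". It does not mention a continuity correction or a one-sided version.

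The protocol amendments section reports the increase from 42 to 62 participants as "resulting in a decrease of the ES from 0.8 to 0.65", again at 80% power. The only directional statement is in the Background: "The MIPS technique is hypothesized to result in a lower incidence of inflammation" than the linear incision technique.

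**The concern.** The value 1.65 is the one-sided 5% normal quantile. A chi-square test on a 2 × 2 table at 0.05 has critical value 3.84 = 1.96² and rejects whichever group has the higher rate. The calculation and the planned test therefore use different critical values, and the trial cannot have 80% power under the test it names.

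Two things are at stake. First, if the test is run as named, a null result on the primary endpoint would be read against 80% power, when the chance of missing the planned effect is about 30% rather than 20%. Second, if the team instead rejects at a one-sided 5%, the false-positive risk in favour of MIPS is 5% rather than the 2.5% that a two-sided 5% test allows, and the text would not have told readers so. Because sidedness is not stated in words, it could also be settled after the data are seen, in an open trial run by the manufacturer.

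**Working it through.** **Inputs.** From the sample size section: alpha 0.05, power 0.80, z-values 1.65 and 0.84, h = 0.65, drop-out 5%. From the allocation section: groups randomized "in a 1:1 ratio for the test and control group stratified for gender".

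**The plan's own figure.** n = 2(1.65 + 0.84)²/h² = 12.40/0.4225 = 29.35 per group. Allowing for drop-out, 29.35/0.95 = 30.9, so 31 per group and 62 in total. The stated figures are reproduced, but only with the one-sided value.

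**Same formula, two-sided.** n = 2(1.96 + 0.8416)²/0.4225 = 37.15 per group. Allowing for drop-out, 37.15/0.95 = 39.1, so 40 per group and 80 in total.

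**Power of the planned size.** Power = Φ(h√(n/2) − z), with h = 0.65. For n = 29.4, h√(n/2) = 0.65 × √14.7 = 2.492. Then Φ(2.492 − 1.96) = Φ(0.53) = 0.703, against Φ(2.492 − 1.645) = 0.802.

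| Evaluable per group | One-sided 5% | Two-sided 5% |
|---|---|---|
| 29 | 79.7% | 69.7% |
| 29.4 | 80.2% | 70.3% |
| 30 | 80.9% | 71.1% |
| 31 (no drop-out) | 82.0% | 72.5% |

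**Effect detectable with 80% two-sided power.** h = (1.96 + 0.8416)/√(n/2). This is 0.73 at 29.4 per group, 0.74 at 29 and 0.71 at 31. As an example, h = 0.73 corresponds to 38.1% against about 8.7%, where 38.1% is the upper end of the PAD range cited in the Background.

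**The design before the amendment.** With effect size 0.8, 12.4/0.64 = 19.4 per group one-sided, which fits 42 participants after drop-out. The two-sided requirement is 24.5 per group. At 20 evaluable per group the two-sided power was 71.6%. The same z-value therefore underlies both sizes.

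**Effect of the continuity correction.** The h formula contains none, although the sample size section names Yates. The table gives exact two-sided power for 29 to 31 per group, found by enumerating all possible 2 × 2 tables. The article gives no event rate for its calculation, so the control rates are assumptions: the two ends of its cited PAD range. The MIPS rate is the one that makes h = 0.65.

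| Assumed control rate | MIPS rate | Plain chi-square | Yates-corrected |
|---|---|---|---|
| 16.1% | 0.8% | 63–67% | 27–32% |
| 38.1% | 11.1% | 68–72% | 57–60% |

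**The case against.** The strongest reply is that a one-sided design was intended. The value 1.65 is printed openly, each later step is correct for it, the hypothesis is directional, and a two-sample test of proportions can be run one-sided. On that reading 80% is right under the formula. The article never uses the word two-sided, so that reading is inferred from the named test. This much stands. However, a directional hypothesis does not make a chi-square test one-sided, and both relevant sections name the non-directional test. An unseen analysis plan may fix the sidedness, but it cannot make the printed 80% agree with the test named beside it.

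A second reply is that 70% is not exact. With no drop-out, power is 72.5%. With the Yates correction it is well below 70%, so printing 70% without settling the test would replace one unsupported figure with another. That is a fair point about the remedy, and the fix below takes it up. It does not weaken the concern: 70% is close to the figure for the plain chi-square, and the corrected test does worse. Nor would declaring the test one-sided rescue 80% if Yates is kept: exact one-sided Yates power is 44–50% at a 16.1% control rate and 69–73% at 38.1%.

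The limitations section does call the small sample a major drawback, but it leaves the 80% claim in place.

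**Conclusion.** The concern holds. The figures 29.4, 31 and 62 follow only from a one-sided 5% critical value, while the planned test at 0.05 is two-sided. Under that test, power at h = 0.65 is about 70% with the expected drop-out and 72.5% without it. The risk of missing the planned effect is therefore about 30%, not 20%. Power of 80% is reached only at an effect of about h = 0.73.

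These figures rest on the arcsine approximation that the plan itself uses, on equal groups, and on reading the chi-square test in its usual two-sided form. Seventy per cent is a favourable figure: applying the Yates correction lowers it further, by an amount that depends on a control rate the article does not give. Because the error sits in the only justification of the sample size for the primary endpoint, and again in the amendment, it should be corrected before the primary analysis.

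**What to change.** 1. State in the sample size and statistical analysis sections, and in the SAP, that the primary test is two-sided at 0.05.
2. Say whether the continuity correction applies, so that the two sections name the same test.
3. Replace the 80% claim in the sample size section and in the amendment text. For the uncorrected test: about 70% power at h = 0.65, or 80% at h of about 0.73, with 29 to 30 evaluable per group. If Yates is kept, give power for that test at stated control and MIPS rates.
4. If a one-sided 5% test is truly intended, declare it, name a directional test, and report a matching 90% confidence interval.

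The cost is wording in the protocol and SAP, and a less favourable stated power. Correcting the statement needs no extra participants or procedures. Recruitment was still open and the SAP was still to be written when the article appeared, so the change could be made before the primary analysis.
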